##### The visual analogue scale for drug craving

The other primary outcome will be the determination of drug craving using a visual analogue scale for drug craving on which the participants will mark on a 100-mm line in proportion to their craving from 0 (no craving) to 100 (strong craving) [21]. The degree of craving will be marked by the subjects at baseline and the 2nd, 4th and 6th weeks after acupuncture administration and at the post-treatment follow-up visit in the 10th week.

#### Secondary outcome

##### The urine test for opioid use

One of the secondary outcome measures will be a positive urine test for opioid use. Subjects will be asked to submit the urine sample at baseline and the 2nd, 4th and 6th weeks after acupuncture administration and at the post-treatment follow-up visit in the 10th week.

##### The 36-item Short Form Survey

The quality of life will be assessed through the Chinese version of the SF-36 from baseline to the 4th, 6th and 10th weeks. Testing of the Chinese version of SF-36 has shown validity similar to that of the original language version [22]. The quality of life is assessed by SF-36 in eight domains: general health (GH), physical functioning (PF), role limitations due to physical problems (RP), role limitations due to emotional problems (RE), bodily pain (BP), social functioning (SF), vitality (VT) and general mental health (MH) [23]. PF, RP, BP, SF and RE will assess the absence of limitations or disability, while the positive state of well-being will be assessed by GH, VT and MH. Subjects who achieve mid-range scores indicate no reported limitations or disabilities [24]. In this study, higher scores will indicate better health status.

##### Pittsburgh sleep quality index (PSQI)

Sleep quality will be assessed using the Chinese version of the PSQI [25] from baseline to the 4th, 6th and 10th weeks. The Chinese version of the PSQI has demonstrated reliability and validity similar to that of the original language version [26]. The PSQI evaluates sleep disturbances through subjective sleep quality, sleep duration, sleep latency, habitual sleep efficiency, sleep disturbances, daytime dysfunction and use of sleeping medication. Each item is graded on 4-point scale (0–3), which is summed together to gain a total score (0 to 21). Higher scores show that patients suffer a higher severity of sleep disturbance, and a total score higher than 5 indicates “poor sleep”.

##### The Beck Depression Inventory-II (BDI-II)

BDI-II, a self-reported questionnaire, will be used to assess the severity of depression, which consists of 21 symptoms [27]. Each symptom is graded on 4-point scale (0–3), which is summed together to yield a total score (0 to 63). Higher scores mean a greater severity of depression. The Chinese version has been validated in adolescents [28]. The BDI-II will be assessed at baseline and the 2nd, 4th, 6th and 10th weeks.

##### The Beck Anxiety Inventory (BAI)

Anxiety symptoms will be assessed by the BAI, which is a 21-item questionnaire [29]. Each symptom is rated on a 4-point scale (0–3). The maximum score is 63, and higher scores indicate greater severity of anxiety. The BAI will be assessed at baseline and at the 2nd, 4th, 6th and 10th weeks.

### Safety

All participants will have some tests to check their body at screening and after 6 weeks of treatment. These tests will be relative to the heart, liver, kidney and other organs, including white blood cell count, haematocrit, haemoglobin, platelets, aspartate aminotransferase/alanine aminotransferase, blood urea nitrogen, creatinine, gamma-glutamyl transpeptidase, erythrocyte sedimentation rate and electrocardiogram.

Adverse events (AEs) are defined as any unexpected unfavourable signs, symptoms or feelings occurring in subjects during the entire period, whether or not associated with JTN treatment. Every AE will be fully recorded on the case report form (CRF), including all details of AEs. Serious AEs that threaten a participant’s life or result in hospitalization will be reported to the Research Ethics Committee concerned within 24 h. All the tests and AEs are recorded, with an aim to evaluate the safety of JTN.

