### Intervention

The interventions will be performed by licensed acupuncturists with more than 3 years of experience in clinics. According to the traditional acupuncture theory and previous RCTs, the acupuncture study interventions were developed by a consensus of acupuncture experts. Before initiation of the study, the acupuncturists will obtain special training to gain total understanding of the treatment and receive a brochure that shows the acupuncture manipulation with detailed information. Subjects who are assigned to the acupuncture group will receive MMT and JTN treatment for 30 min per session. Meanwhile, those who are randomized to the routine group will receive MMT only. All 18 sessions of JTN treatment will be delivered over 6 weeks (3 per week) and followed by a 4-week follow-up period. The study schedule is shown in Fig. 2.

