**Fig. 3 Fig3:**
[figure not shown]
Acupuncture points used in the study

Sterile stainless-steel disposable acupuncture needles (Huatuo, Suzhou, China; lengths and diameters 0.3 mm × 25 mm or 0.3 mm × 40 mm) will be used in this group. Among the points we choose, *Shouzhi-zhen* will be needled at an angle of 45–90° to the participant’s skin*,* while *Dingshen-zhen* and *Sishen-zhen* will be needled at an angle of 15–30° to the skin. The needles will be inserted at a depth of 5–30 mm. After that, the needles are stimulated manually to achieve the typical acupuncture sensation of *de qi*, which is characterized as soreness, numbness and heaviness. During every session, the acupuncture needles will be retained for 30 min and twirled every 10 min. JTN treatment will be discontinued if the patients suffer from any adverse events, and the acupuncture physicians can decide to terminate the trial.

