#### Routine group

All participants in the control group will receive only MMT; they will not receive any treatment related to acupuncture after randomization for 10 weeks. During the study period, there will be five face to face visits and a diary will be collected. After the trial, all participants will have a chance to receive JTN treatment for 6 weeks as compensation.

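### The adverse-event definition admits only unexpected events, so foreseeable needling reactions could go uncounted and the adverse-event frequency under JTN could be understated

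*Protocol article*

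**What the plan says.** The Safety section of the protocol article gives this definition: "Adverse events (AEs) are defined as any unexpected unfavourable signs, symptoms or feelings occurring in subjects during the entire period", and adds "whether or not associated with JTN treatment". On recording it says: "Every AE will be fully recorded on the case report form (CRF), including all details of AEs". It closes by stating that the laboratory tests, the electrocardiogram and the adverse events are together the basis for judging the safety of JTN.

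Two other places depend on this definition. In the Acupuncture group section, the paragraph on needling below Fig. 3 says that the needles are stimulated to reach a sensation "characterized as soreness, numbness and heaviness". The same paragraph makes the occurrence of any adverse event a reason to stop JTN. The Intervention section sets the exposure: "All 18 sessions of JTN treatment will be delivered over 6 weeks (3 per week"). Safety is named as an aim beside efficacy in the Abstract, the Background and the Study design section.

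**The concern.** Expectedness is normally an attribute that is assigned to an adverse event after it has been recorded. Here it stands in the definition and decides whether the event is recorded at all. The events that a safety assessment of needling most needs to count are the foreseeable local and general reactions to needling, and a literal reading leaves these out. The article does not list which reactions are expected, so each person who completes a form must decide alone. Practitioners and participants know the allocation.

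For needling reactions the filter acts in one direction, because only the JTN arm is needled during the study. A low adverse-event count in that arm could then mean good tolerability, or it could be a product of the definition, and the reader of the final report could not tell which. Withdrawal and methadone effects can occur in both arms, so the direction of any distortion between arms is not known for them.

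**Working it through.** No stated figure is at issue, so there is none to reproduce. The check is textual, followed by an illustration of scale.

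**1. What the definition admits.** It has two separate qualifiers. The clause "whether or not associated with JTN treatment" removes any condition on relatedness. The word *unexpected* imposes a condition on expectedness. Widening the first does not loosen the second:

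| Event | Related to JTN | Expected | Inside the literal definition |
|---|---|---|---|
| Unforeseen reaction to needling | yes | no | yes |
| Unforeseen intercurrent illness | no | no | yes |
| Foreseeable reaction to needling | yes | yes | no |
| Foreseeable withdrawal or methadone effect | either | yes | no |

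The promise to record every adverse event does not help in the last two rows, because it applies only to events that already meet the definition.

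**2. Whether another route captures the excluded events.** The blood tests and electrocardiogram are done at screening and after 6 weeks, and would not show a transient reaction to a session. Among the outcomes, the anxiety, depression and sleep scales touch on some withdrawal complaints. No withdrawal scale is listed, although the Background describes withdrawal symptoms and a wide range of methadone side effects, and the trial hypothesises lower methadone use. No section provides for recording needling reactions separately.

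**3. The link to the needling paragraph.** Two consequences follow.
- The sought sensation includes soreness and numbness, and the text does not say when such a sensation becomes an unfavourable event.
- Stopping of JTN depends on the same term. Under the current wording, a reaction judged to be expected is not recorded and does not trigger stopping. If the definition is widened and nothing else changes, every minor reaction would meet the stated condition for stopping. The Safety section and the needling paragraph therefore have to be changed together.

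**4. Scale, on assumed rates.** Inputs from the document: 70 participants in the acupuncture group (Study design; Sample size calculation) and 18 sessions each (Intervention). Assumption: a rate p of foreseeable reactions per session, with sessions independent and all of them delivered.

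Sessions = 70 × 18 = 1,260. Expected reactions = 1,260 × p. Proportion of participants with at least one = 1 − (1 − p)^18.

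| Assumed p | Reactions outside the definition | Participants with at least one |
|---|---|---|
| 1% | 12.6 | 17% |
| 2% | 25.2 | 30% |
| 5% | 63 | 60% |
| 10% | 126 | 85% |

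The table shows only that, with 18 sessions per person, even a low rate per session could matter. It is not an estimate for this trial.

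**The case against.** The strongest reply is that *unexpected* is loose wording for untoward. The rest of the definition is broad: it covers signs, symptoms and feelings of any cause over the whole study. The Background even claims that acupuncture for opioid dependence has no side effects. On the protocol's own view, then, no needling harm is expected, and bruising or faintness would count. The word may also be meant only to set aside the sensation that the acupuncturist seeks, which is reasonable. This much stands: the article nowhere says that known reactions are to be left out, so undercounting is a possible result of following the text and not a stated intention. The reply does not remove the ambiguity, because the word decides what is counted and is not explained.

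A second reply is that the article condenses a full protocol, which the Data Availability section offers on request. That would answer a complaint about a missing detail. Here the article states a definition, and the definition as stated is too narrow.

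Three stronger readings are tempting, and the document does not support them.
- **Death in the 24-hour rule.** The rule reads: "Serious AEs that threaten a participant’s life or result in hospitalization will be reported to the Research Ethics Committee concerned within 24 h". Death is not named, and a reader might infer that deaths would be lost. The rule governs reporting to the ethics committee and not what is recorded, so it changes no adverse-event count. Fuller seriousness criteria may stand in the full protocol.
- **Unequal contact.** A reader might set 18 sessions against the routine group's text, "there will be five face to face visits and a diary will be collected", and infer that events are far more likely to be noticed under JTN. The section on daily consumption of methadone says that enrolled patients attend the clinic daily, which applies to both arms. A diary mentioned under one arm is not shown to be absent from the other.
- **Most harms missed.** A reader might infer that most needling harms would go unrecorded and that the safety conclusion is bound to be too favourable. That would need reaction rates and a known recording practice, and the article gives neither.

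**Conclusion.** The point holds in a limited form. As written, the definition makes expectedness a condition for counting an event, and no other part of the article captures the foreseeable events that it leaves out. If it is applied literally, adverse-event frequency could be understated, particularly in the JTN arm, for a stated aim of the trial. The size cannot be determined from the document. The range of about 13 to 126 uncounted reactions rests wholly on assumed rates of 1% to 10% per session and full attendance. The conclusion assumes that staff apply the word as it stands; if they read it as untoward, little or nothing is lost. The primary efficacy outcomes are not defined by this wording.

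**What to change.** Delete *unexpected* from the definition in the Safety section. Record every unfavourable occurrence in both arms over the whole study period, whether or not related to JTN, and code expectedness and relatedness as two separate fields on the case report form. Expected events can then be tabulated apart from unexpected ones without being lost.

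In the same revision, reconcile the Acupuncture group section with the new definition. State how the sought needling sensation is distinguished from an unfavourable event, and have the investigators bring the condition for stopping JTN and the revised definition into agreement. Which stopping rule is right is a clinical decision outside this review.

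The cost is a wording change in the protocol, two form fields and a short instruction to the staff who record events. More minor events will be listed for JTN, which follows from counting them. Recruitment began on 5 October 2019, so for participants already treated, the report should say from what date the wider definition applied.

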### Quality control, data management and monitoring

Before recruitment, the entire team will be required to attend a training workshop, which ensures their strictly compliance with the study protocol and total understanding of the trial administration process. The interventions will be performed by licensed acupuncturists with more than 3 years of experience in hospitals or clinics. They will also receive a brochure about the protocol and standard operating procedures of JTN.

The data will be carefully collected and recorded on CRFs. All data will be put onto a computer with password protection by staff blinded to the group allocation and checked twice by investigators after data entry. Data quality will be checked regularly by research assistants and supervised by monitors. The original CRFs and all other forms will be archived securely at the Medical College of Acu-Moxi and Rehabilitation of Guangzhou University of Chinese Medicine. The South China Research Center of Guangzhou University of Chinese Medicine will be responsible for monitoring for the data, regulatory management of this trial, auditing the trial every 3 months independently of investigators and the sponsor and deciding on any premature closure of the study.

### Sample size calculation

The primary outcome measure for drug craving is VAS. Based on previous studies [5, 30], after 4 weeks of treatment, the VAS for drug craving score difference between the baseline and the endpoint in the sham acupuncture group should be approximately 20 ± 30, while the true acupuncture group should be approximately 37.5 ± 28. Type 1 error is assumed at 0.05, and type 2 error is assumed at 0.1. PASS11.0 software (CSS Statistical Software, Kaysville, UT, USA) has been used to determine the sample size, and the minimum sample size is 60 subjects for each group. Considering a dropout rate of 15%, a total of 140 subjects will be required with 1:1 allocation to each group (70 participants per group) for this study.

### Statistical analysis

All analyses will be conducted based on the intention-to-treat principle and per-protocol (PP) analysis. Missing data will be replaced according to the principle of multiple imputations. Descriptive statistics will be presented for each group as the mean change (SD, 95% confidence intervals). All statistical tests will be analysed by using the SPSS statistical software version 20 (IBM SPSS Statistics, New York, USA). *P* values < 0.05 (two-sided) are considered statistically significant. Demographic and baseline data will be tabulated and evaluated using analysis of variance (ANOVA) or the *χ*^2^ test. To compare means between two groups, we will use the independent sample *t* test. Two-way repeated-measures analysis of variance (ANOVA) will be carried out to explore time × treatment interaction (“time” is the unit of measurement).

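### The stated summary and outcome methods do not suit the yes/no urine result: they give neither the percentage positive by arm nor a baseline-adjusted treatment effect

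*Protocol article*

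**What the plan says.** All wording is from the protocol article.

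- The urine test for opioid use: "One of the secondary outcome measures will be a positive urine test for opioid use". Samples are taken at baseline and at weeks 2, 4, 6 and 10.
- Statistical analysis, summaries: "Descriptive statistics will be presented for each group as the mean change (SD, 95% confidence intervals"). No outcome is exempted.
- Statistical analysis, comparisons: an independent-sample t test where means are compared, and a two-way repeated-measures ANOVA directed at the time-by-treatment interaction.
- Statistical analysis, the only method for categories: "Demographic and baseline data will be tabulated and evaluated using analysis of variance (ANOVA) or the" chi-square test. It is tied to demographic and baseline data.

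No post-baseline method for a binary outcome is named. No urine-positive rate, no correlation between visits and no single analysis visit for urine are given.

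**The concern.** The section does more than stay silent. It fixes one summary for all outcomes, and that summary does not fit this one. Applied to urine, each patient's change is −1, 0 or +1, and a mean and SD of such values do not tell a reader what share of each arm tested positive. The outcome methods listed are all for means, and none yields a treatment effect on the proportion positive adjusted for the baseline result, although that result is collected.

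The outcome deserves a good analysis. Patients and practitioners know the allocation (Randomization, allocation and concealment). Craving is self-marked: "The degree of craving will be marked by the subjects at baseline" and at each later visit. The other scales are questionnaires, and the methadone dose is controlled by a doctor. Urine is the one laboratory-type efficacy measure, so it is a natural check on whether lower craving or methadone use goes with less illicit use or with more. That is an inference from the design; the article does not say it.

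**Working it through.** **The plan's own figure.** It concerns craving only. Inputs: "Type 1 error is assumed at 0.05, and type 2 error is assumed at 0.1"; "values < 0.05 (two-sided) are considered statistically significant"; change "in the sham acupuncture group should be approximately 20 ± 30", "while the true acupuncture group should be approximately 37.5 ± 28".

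n per group = (1.960 + 1.282)² × (30² + 28²) / (37.5 − 20)² = 10.51 × 1684 / 306.25 = 57.8, so 58, or 59 with the t distribution. The stated 60 is reproduced. With 15% dropout, 60 / 0.85 = 70.6, against the stated 70 per group. About 70 × 0.85 = 59.5 patients per arm would be evaluable, so 60 is used below.

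**Is a t test on 0/1 data wrong?** No. Simulated at 60 per arm, its type I error is 0.046–0.054 and its power is within about 1 point of the chi-square test.

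**Precision by formula (assumed rates).** Take 40% positive in the routine arm and 25% in the acupuncture arm, and 40% in both at baseline. Then v0 = 0.40 × 0.60 = 0.24, v1 = 0.25 × 0.75 = 0.1875, and v0 + v1 = 0.4275. Let r be the correlation between two 0/1 results in one patient. Power = Φ(0.15/SE − 1.96), with SE² as follows:

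- change score at one visit: [2·v0·(1 − r) + v0 + v1 − 2r√(v0·v1)] / 60
- one visit, unadjusted: (v0 + v1) / 60
- one visit, baseline-adjusted: (v0 + v1)(1 − r²) / 60
- mean of weeks 2, 4 and 6, unadjusted: (v0 + v1)(1 + 2r)/3 / 60
- the same mean, baseline-adjusted: (v0 + v1)[(1 + 2r)/3 − r²] / 60

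| Analysis | r = 0.4: SE (points), power | r = 0.7: SE (points), power |
|---|---|---|
| Change score | 9.5, 35% | 6.8, 60% |
| One visit, unadjusted | 8.4, 43% | 8.4, 43% |
| One visit, adjusted | 7.7, 49% | 6.0, 70% |
| Three-visit mean, unadjusted | 6.5, 63% | 7.5, 51% |
| Three-visit mean, adjusted | 5.6, 76% | 4.7, 89% |

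Example, first row at r = 0.4: (0.288 + 0.258)/60 = 0.0091, SE = 0.095, power = Φ(1.57 − 1.96) = 35%.

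The change score is noisier than the single visit when r is below about 0.5. It overtakes the *unadjusted* three-visit mean above about r = 0.65. Pooling visits alone is therefore not always better; adding the baseline result is what makes the advantage consistent.

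**Simulation, same rates, constant effect.** Each patient's results come from correlated normal variables cut at the stated rates; the adjusted analyses are linear regressions on arm and baseline result, standing in for the GEE. The latent correlation runs from 0.3 to 0.9, which corresponds to about 0.19 to 0.71 between the 0/1 results. Simulation error is about 1 point.

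| Analysis | Power |
|---|---|
| Change score | 28–57% |
| One visit, unadjusted | about 41% |
| One visit, baseline-adjusted | 43–67% |
| Mean of weeks 2, 4 and 6, baseline-adjusted | 75–86% |

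**If the effect builds up to week 6** (for example 35%, 30%, then 25% positive in the acupuncture arm), the adjusted average falls to about 41–53%, while week 6 with baseline adjustment keeps 43–67%.

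**The stated ANOVA.** It does use all visits, but it tests the interaction. For 50% v 30%, 40% v 20% and 30% v 15% with all five visits, its simulated power is 33–49% at a 0/1 correlation of about 0.3, 44–63% at 0.5 and 61–82% at 0.7. A baseline-adjusted average of the four later samples has 89–98% over the same range. If baseline were left out and the effect were constant, the interaction test would have about 5% power, because there would be no interaction to find.

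**The case against.** The strongest reply is that this is mostly silence. The t-test sentence is limited to comparing means, and a positive test is not a mean, so the section may simply not address urine. A journal article condenses a fuller protocol, which Data Availability says exists, and an analysis plan may name a binary method. This stands as far as the missing test goes: absence of a binary model from the article is not itself a fault. It does not answer the descriptive summary, which is fixed without exception and does not suit a yes/no result.

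Four stronger readings are tempting and should be resisted:

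- *That the plan prescribes a week 6 change-score t test for urine.* It does not. The change to week 6 is specified for methadone only; the change-score figures above show what a literal reading would cost.
- *That treating 0/1 data as means invalidates the test.* The type I error stays near 5%.
- *That a real reduction would more likely than not be missed.* This depends on the assumed rates. For 40% v 20%, the formulas give 69% power for one unadjusted visit and 45–74% for the change score over r = 0.2 to 0.6.
- *That pooling visits always wins.* Without baseline adjustment the ranking reverses above r of about 0.65, and a late effect removes most of the gain.

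The choice between week 6 and an average is also partly one of preference; either is defensible if fixed in advance.

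**Conclusion.** The point holds in limited form. The article's summary and named outcome methods do not suit the binary urine result: they do not report the percentage positive by arm, and they provide no baseline-adjusted treatment effect from the five samples collected. The consequence is lost precision and readability in one secondary outcome. Neither primary outcome nor the sample size is affected, and false positives are not inflated.

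Baseline adjustment improved on both the change score and the unadjusted visit throughout the range simulated. The further gain from averaging weeks 2, 4 and 6 is large only if the effect is present from week 2. All power figures assume 60 evaluable per arm and urine rates and correlations that the article does not supply, so they indicate direction and rough scale only. The point is worth correcting, in proportion to a secondary outcome.

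**What to change.** In Statistical analysis, restrict the mean-change summary, the t test and the ANOVA to continuous outcomes, and add a paragraph for urine along these lines:

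- Report the number and percentage positive by arm at every visit.
- Fit one logistic generalised estimating equation model to the post-baseline results, with arm, visit, arm × visit and baseline result as terms and robust standard errors.
- Prespecify one contrast, given as a difference in percentage positive with 95% CI: either week 6, which matches the primary methadone time point, or the average over weeks 2, 4 and 6.
- Report the remaining visits, including week 10, as supportive.

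If a fuller protocol or analysis plan already contains such a model, it is enough to limit the mean-change sentence to continuous outcomes and point to that model.

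Cost: a paragraph of text and a little more analysis work, with no new data, visits or patients. If the average is chosen, an effect that appears late is diluted; the by-visit percentages would still show it. The choice should be made before allocation is revealed to the statisticians.

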**Methods/design:**

This study is a parallel-arm, randomized controlled trial that aims to evaluate the efficacy and safety of acupuncture as adjunctive therapy for patients receiving MMT. A total of 140 eligible participants who range in age from 18 to 60 years and fulfil the Diagnostic and Statistical Manual of Mental Disorders, 5th edition (DSM-V), for opiate dependence will be enrolled into this study. All eligible participants will be randomly assigned to the acupuncture group or routine group in a 1:1 allocation ratio. Participants who are enrolled in the acupuncture group will receive MMT and JTN treatment for 30 min per session. Meanwhile, those who are assigned to the routine arm will receive MMT only. All 18 sessions of JTN treatment will be delivered over 6 weeks (3 per week) and followed by a 4-week follow-up period. The primary outcome measure will be the visual analogue scale (VAS) for drug craving and the daily consumption of methadone (DCOM). Secondary outcome measures will include the urine test for opioid use, the 36-item Short Form Survey (SF-36), the Beck Anxiety Inventory (BAI), the Beck Depression Inventory II (BDI-II) and Pittsburgh sleep quality index (PSQI). VAS, DCOM, BAI, BDI-II and the urine test for opioid use will be evaluated at baseline, the second week, the fourth week, the sixth week and the tenth week. SF-36 and PSQI will be assessed at baseline, the fourth week, the sixth week and the tenth week.

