### Outcome

#### Primary outcome

##### The daily consumption of methadone

Daily consumption of methadone from baseline to the 2nd, 4th, 6th and 10th weeks will be presented. One primary outcome measure will be the change in the daily consumption of methadone from baseline to the 6th week. The enrolled patients will go to the clinic to receive methadone every day, and the dosage will be strictly administered by the doctor, which will be recorded in the clinic computer system.

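### Two primary outcomes share one unadjusted 0.05 threshold, and no rule says whether one or both must be significant for the trial to succeed

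*Protocol article*

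**What the plan says.** The abstract of the protocol article (Methods/design) gives both outcomes primary status: "The primary outcome measure will be the visual analogue scale (VAS) for drug craving and the daily consumption of methadone (DCOM"). The Primary outcome section repeats this. For methadone: "One primary outcome measure will be the change in the daily consumption of methadone from baseline to the 6th week". For craving: "The other primary outcome will be the determination of drug craving using a visual analogue scale for drug craving". The craving entry lists measurements at baseline and weeks 2, 4, 6 and 10 and singles out none of them.

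Under Sample size calculation, the only outcome used is craving ("The primary outcome measure for drug craving is VAS"), with changes assumed after 4 weeks of treatment. The error rates are set once: "Type 1 error is assumed at 0.05, and type 2 error is assumed at 0.1". No effect or SD is given for DCOM.

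Under Statistical analysis, the significance rule for all tests is that "values < 0.05 (two-sided) are considered statistically significant". On analysis sets, it says: "All analyses will be conducted based on the intention-to-treat principle and per-protocol (PP) analysis". No section ranks the two outcomes, divides the 0.05 between them, or says what pattern of results makes the trial positive.

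**The concern.** With two primary outcomes, the error rate and the power of the trial depend on how the two tests are combined. The protocol states the ingredients (two primaries, 0.05 for each test, power 90% on one of them) but not the combination.

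If a significant result on either outcome supports a positive claim, there are two chances of a false positive at 0.05 each, and the 5% in the sample size section is not the trial's type 1 error. If both must be significant, the error rate is safe, but the 90% in the same section is not the trial's power. Under either reading one of the two stated design figures does not describe the trial.

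The open choice could also be made after the results are known. The trial is open-label and craving is marked by patients who know their allocation, so a success rule settled late would be hard to defend.

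**Working it through.** **Inputs from the protocol article.** Two primary outcomes (abstract; Primary outcome). Two-sided 0.05 for each test and an independent-sample t test (Statistical analysis). VAS change: control 20, SD 30 ("sham acupuncture group should be approximately 20 ± 30"); acupuncture 37.5, SD 28; type 2 error 0.1; 60 evaluable per group (Sample size calculation).

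**Assumed.** The correlation r between the two test statistics is not given; the range 0 to 0.9 is shown. DCOM power is not given; 90% is used for illustration only.

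**1. The plan's own figure.**
- Difference: 37.5 − 20 = 17.5.
- Pooled SD: √((30² + 28²)/2) = √842 = 29.02.
- Normal approximation: n = 2 × 842 × (1.960 + 1.282)² / 17.5² = 57.8, so 58 per group.
- Noncentral t: 59 per group; power at 60 per group is 90.6%.
- A one-sided 0.05 would give 48 per group.

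The stated 60 is reproduced to within two patients, and only with the full two-sided 0.05 spent on VAS.

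**2. Either outcome counts as success.** With independent tests, the error is 1 − (1 − 0.05)² = 1 − 0.9025 = 9.75%. With correlated tests, it is 1 − P(|Z1| < 1.96 and |Z2| < 1.96) under a bivariate normal:

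| r | Chance of at least one false positive |
|---|---|
| 0 | 9.75% |
| 0.3 | 9.5% |
| 0.5 | 9.1% |
| 0.7 | 8.3% |
| 0.9 | 7.0% |

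**3. Both outcomes required.** The chance of a false claim is at most 5%, so there is no inflation. Joint power needs a DCOM effect and SD, which the article does not give. If DCOM also had 90% power, joint power = P(both tests significant):

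| r | Joint power |
|---|---|
| 0 | 0.90 × 0.90 = 81% |
| 0.5 | 83% |
| 0.9 | 87% |

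With lower DCOM power, these figures would be lower.

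**4. What control would cost VAS.**
- At two-sided 0.025 (a Bonferroni split, or the first step of Holm), VAS power at 60 per group is 84.8% against 90.6% at 0.05.
- An equal split gives a familywise error of 1 − 0.975² = 4.94% with independent tests.
- Restoring 90% VAS power at 0.025 would need 70 evaluable per group, which is 70/0.85 = 82.4, so 83 per group with 15% dropout.
- A fixed sequence with VAS first leaves VAS at 0.05 and its power at 90.6%, under the 4-week assumptions.

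**The case against.** The strongest objection is that the inflation is conditional. A reader might infer that the trial's false-positive rate simply is nearly double 5%. The article does not support that. It never says that one significant outcome is enough; the abstract joins the two with a plain conjunction, and the Background hypothesises reductions in both craving and methadone need. Under a both-required rule there is no inflation. Even under an either-outcome rule, 9.75% is the figure for independent tests and falls to 7.0% at correlation 0.9. This part of the objection stands.

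It can also be said that this is a condensed article and that a multiplicity procedure may sit in the full protocol or an SAP. That carries less weight. The article is not silent: it states a blanket 0.05 rule and a sample size that spends all of it on one of two primaries. A later document that added control would have to qualify that rule.

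A reader might also infer that the per-protocol analysis can remove patients for missed sessions in the acupuncture arm only. That presumes a per-protocol definition the article does not give. Routine-arm patients could also deviate, for example by having acupuncture or missing visits. This inference is not part of the point.

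Finally, the order of the outcomes is the trial team's choice. VAS is the sized outcome, but DCOM is the one with an explicit primary time point and is recorded by the clinic system.

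**Conclusion.** The concern holds in conditional form. Two primary outcomes, one unadjusted two-sided 0.05 threshold and a sample size built on VAS alone leave the meaning of a positive trial undefined.

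- If either outcome suffices, the type 1 error is about 7.0% to 9.75%, assuming a correlation of 0.9 to 0, against the stated 5%.
- If both are required, the error is at most 5% and the stated 90% power is for VAS only. Joint power is not computable from the article; 81% to 87% applies only if DCOM also had 90% power, over the same correlations.

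The 90.6% VAS power reproduced here takes the protocol's 4-week change figures at face value. It is not shown to hold at week 6, the time point given for DCOM.

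**What to change.** Before unblinding, prespecify one confirmatory procedure on the intention-to-treat set that holds the familywise error at two-sided 0.05. There are two suitable forms:

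- **Fixed sequence.** For example, test VAS first at 0.05, as the sized outcome, and test DCOM change to week 6 at 0.05 only if VAS is significant. The cost is that the second outcome cannot be claimed if the first fails.
- **Holm** across the two outcomes. Either can be claimed alone. The cost is that VAS power at 60 per group can fall from 90.6% to as low as 84.8%.

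Name a single primary time point for VAS. If week 6 is chosen to match DCOM, state that the 90% power rests on carrying the 4-week assumptions over to week 6. Label per-protocol results, other visits and secondary outcomes as supportive.

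If the team in fact intends that both outcomes be required, it should say so. Each test then stays at 0.05, and a DCOM effect and SD should be given so that joint power can be stated.

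The change takes a few sentences and, for the fixed sequence or Holm, no additional patients.
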